### Intervention

2.6

This trial consists of a screening phase (1 week), a treatment phase (4 weeks), and a post-treatment follow-up phase (12 weeks). During the treatment period, participants in the verum acupuncture plus placebo group will receive 12 sessions of verum acupuncture treatment and itopride placebo tablets for 20 days. Patients in the itopride plus sham acupuncture group will take itopride tablets for 20 days and receive 12 sessions of sham acupuncture treatment. Patients in the sham acupuncture plus placebo group will take itopride placebo tablets for 20 days and receive 12 sessions of sham acupuncture treatment. The detailed treatment procedures is as follows:

#### Verum or sham acupuncture

2.6.1

In the verum acupuncture protocol, acupoints of SiBai (ST2), Liangmen (ST21), Zusanli (ST36), Neiguan (PC6), and Gongsun (SP4) were selected based on our prior clinical research on acupuncture for FD (22). The location of all acupoints is followed the Nomenclature and location of acupuncture points per the Chinese National Standard (GB/T22163-2008) and illustrated in Figure 2 and detailed in Table 1. The depth of needle penetration will vary depending on the location of acupoints, refer to Table 1 for details. Before inserting the needle into the skin, acupuncturists will sterilize both the needle (Huatuo brand, Suzhou Medical Supplies Factory, China) and the skin, and an adhesive plaster with plastic rings will be fixed on the skin of acupoints. After the needles penetrate the skin, acupuncturists will manipulated them with lifting, inserting, or twisting movements until patients feel the Deqi sensation. The needles will be stay in place for 30 min, during which they will be manually stimulated every 10 min to elicit the needle sensation.

**Figure 2 fig2:**
[figure not shown]
Stimulation points. ST2, Sibai; ST21, Liangmen; ST36, Zusanli; PC6, Neiguan; SP4, Gongsun.

**Table 1 tab1:** Locations and manipulations of acupoints.

Acupoint	Location	Depth of needle penetration in verum acupuncture treatment
Sibai (ST2)	In the face, directly below the pupil, and in the depression of the infraorbital foramen.	Inserted perpendicularly at 0.5 cun with 0.25 mm*25 mm acupuncture needles.
Liangmen (ST21)	In the abdomen, 4 cun above the umbilicus, and 2 cun lateral to the anterior midline.	Inserted perpendicularly at 0.8–1.2 cun with 0.3 mm*40 mm acupuncture needles.
Neiguan (PC6)	In the flexor aspect of the forearm, between the tendons of palmaris longus and flexor carpi radialis, 2 cun above the transverse crease of the wrist.	Inserted perpendicularly at 0.5–0.8 cun with 0.25 mm*25 mm acupuncture needles.
Zusanli (ST36)	In the anterior aspect of the lower leg, 3 cun directly below Dubi (ST35), and one finger-breadth lateral to the anterior border of the tibia.	Inserted perpendicularly at 1–1.5 cun with 0.30 mm * 50 mm acupuncture needles
Gongsun (SP4)	In the anterior and inferior of the base of the first metatarsal bone, and on the dorso-ventral boundary.	Inserted perpendicularly at 0.5–0.8 cun with 0.25 mm*25 mm acupuncture needles

1 cun is defined as the width of the interphalangeal joint of the patient’s thumb. Dubi (ST35) is in the lateral depression of the patellar ligament when the knee is flexed.

In the sham acupuncture protocol, Streitberger needles will be applied at the same acupoints as those used in the verum acupuncture treatment. The Streitberger needle is a non-penetrating acupuncture placebo device that has been well validated. Although its appearance closely resembles that of real needles, the needle tip is blunt. Furthermore, the Streitberger needle features a special handle that enables the blunt needle to press against the skin surface and retract into the handle rather than penetrate the skin. Nonetheless, a pricking sensation similar to that of actual needle insertion will be generated in the skin at the acupoint during this process. Comprehensive details regarding the verum/sham acupuncture method and needle sizes can be found in Figure 3.

**Figure 3 fig3:**
[figure not shown]
Verum vs. sham acupuncture. Sharp needles are punctured subcutaneously in verum acupuncture, while blunt needles are not punctured subcutaneously in sham acupuncture.

The treatment frequency of verum acupuncture or sham acupuncture will be 3 times a week for 4 consecutive weeks, a total of 12 sessions.

#### Itopride or placebo

2.6.2

Patients assigned to the itopride plus sham acupuncture group will take 50 mg of itopride orally 3 times a day, 5 days per week, for 4 weeks. Participants in the verum acupuncture plus placebo group and sham acupuncture plus placebo group will receive an itopride placebo that is identical in taste and appearance to actual itopride tablet; they will follow the same frequency and dosage as the itopride plus sham acupuncture group. All patients are instructed to maintain a medication diary to document their usage and return unused medication.

### Outcome

2.7

Primary outcomes in this study include the proportion of responders (PR) and the elimination rate of the main symptom. The secondary outcomes include changes in symptom score, QOL, mood during the treatment and follow-up, and the participants’ expectancy for acupuncture before treatment, as well as related hormone concentrations. Table 2 display a summary of all measurements. Follow-up for all participants can be completed via social media (WeChat) or phone.

**Table 2 tab2:** SPIRIT figure for the schedule of enrollment, interventions, and assessments.

	Study period								
	Enrolment	Allocation	Treatment phase				Follow-up		
Timepoint**	*1w*		*2w*	*3w*	*4w*	*5w*	*9w*	*13w*	*17w*
Enrolment									
Eligibility screen	X								
Informed consent	X								
Allocation		X							
Interventions									
Verum acupuncture plus placebo									
Itopride plus sham acupuncture									
Sham acupuncture plus placebo									
Assessments									
Proportion of responders			X	X	X	X	X	X	X
Elimination rate			X	X	X	X	X	X	X
NDSI		X				X	X	X	X
SF-NDLQI		X				X	X	X	X
HADS		X				X	X	X	X
Acupuncture expectation		X							
Related hormone concentrations		X				X			
Adverse events			X	X	X	X			

SPIRIT, standard protocol items: recommendations for interventional trials; NDSI, the nepean dyspepsia symptom index; SF-NDLQI, the short form - Nepean Dyspepsia Life Quality Index; HADS, Hospital Anxiety and Depression Scale.

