**Methods:**

This study is a multicentre, double-dummy, single-blind, randomized, active-controlled trial. Two hundred and one eligible participants will be randomly assigned into three groups: a verum acupuncture plus placebo group, an itopride plus sham acupuncture group, and a sham acupuncture plus placebo group. This study consists of a 1-week screening period, a 4-week treatment period, and a 12-week follow-up period. During the intervention period, participants will receive 12 sessions of verum or sham acupuncture treatment (one session per day, three sessions per week, for 4 weeks) along with 50 mg itopride tablets or 50 mg itopride placebo tablets 3 times a day for 20 days (5 continual days a week for 4 weeks). The response rate (patients who had adequate relief of gastric symptoms will be considered positive responders) and the elimination rate of cardinal symptoms (postprandial fullness and early satiation) are the primary indicators to evaluate the overall acupuncture effect for PDS. Secondary outcome measures will include the Nepean Dyspepsia Symptom Index (NDSI), the short form-Nepean Dyspepsia Life Quality Index (SF-NDLQI), the Hospital Anxiety and Depression Scale (HADS), and related hormone concentrations. Participants’ expectations toward acupuncture treatment will also be assessed, and adverse events will be recorded for safety assessment. All analyses will adhere to an intention-to-treat principle.

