### Randomization, allocation, and concealment

2.4

A research assistant at each clinical institution will conduct random assignments independently from other study activities. Eligible patients will be randomly assigned into the verum acupuncture plus placebo group, itopride plus sham acupuncture group, and sham acupuncture plus placebo group in a 1:1:1 ratio. A professional statistician will utilize SAS software (v9.3) to produce a list of random numbers stratified by clinical institution using block sizes of 6 or 9. The randomization process will be carried out through an online central randomization system. The randomization number and group assignment provided to each patient by the randomization system will be unique and unchangeable, ensuring fairness in treatment allocation.

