#### Primary outcome

2.7.1

**The proportion of responders (PR)** Patients experiencing sufficient alleviation of stomach discomfort are categorized as positive responders (23). Participants will be requested to evaluate changes in their symptom relief over the preceding 7 days via a 7-point Likert scale. This scale features options such as “extremely worsened,” “worsened,” “slightly worsened,” “no change,” “slightly improved,” “improved,” or “extremely improved,” which correspond to scores ranging from 0 to 6. Those participants who report a relief score of either 5 or 6 points will be deemed positive responders. The measurement of PR will take place at weeks 2, 3, 4, 5, 9, 13, and 17.

**The elimination rate (ER)** ER refers to the proportion of patients whose main symptoms have disappeared. According to Rome IV criteria, we define postprandial fullness and bloating as the main symptoms. Included patients should have at least one of these symptoms. Using a 7-point Likert scale, the main symptoms are considered to have disappeared if the rating drops to 0 after treatment. ER will be measured at weeks 2, 3, 4, 5, 9, 13, and 17.

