### Sample size calculation

2.11

The sample size for this study was determined based on the responder proportion at the end of a 4-week treatment, with 70.69% for the acupuncture treatment and 55.46% for the itopride treatment, as reported in a previous study (30). The sample size calculation was performed using PASS 15.0 software, with a 1:1 ratio between the verum acupuncture plus placebo group and itopride plus sham acupuncture group. A statistical power of 80% (*β* = 0.2), a one-sided alpha of 0.025 (*α* = 0.025), and a non-inferiority margin of −10% (*Δ* = −10%) were considered in the calculation. The resulting sample size was 57 for each group. Accounting for a 15% dropout rate, each group needed 67 cases, resulting in a total enrollment of 201 cases across three groups.

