### Statistical analysis

2.12

Efficacy analyses will be performed on all patients who were randomized, adhering to the intention-to-treat principle. This approach ensures that all patients are included in the analysis based on the group to which they were initially assigned, regardless of whether they completed the study as intended. Missing data on the primary outcome will be imputed using the multiple imputation method under the missing at-random assumption. If there are significant differences in baseline variables between the two groups, those unbalanced variables will be included as covariates in the analysis of the primary outcome.

We will establish confidence intervals at a 95% level, with a significance level set at 0.05. Continuous data will be reported as mean ± standard deviation (SD) if it is normally distributed. Otherwise, it will be reported as median (interquartile range). For longitudinal continuous data, we will compare groups using repeated-measures analysis of variance (ANOVA), taking into account both group and time-group interactions. Student’s t-test or Wilcoxon rank-sum test will be used for other continuous data. For categorical data, Χ^2^ test or Fisher’s exact test will be applied as appropriate. The strength of linear relationships between variables will be evaluated using linear correlation analysis, and sensitivity analysis will be performed if required. The occurrence of AEs between groups will be summarized using descriptive analysis.

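### PR and ER are both primary at an unadjusted 0.05 with no stated relation, and the one test that sized the trial is not carried into the outcome and analysis sections

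*Protocol article*

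**What the plan says.** **Outcomes.** Section 2.7: "Primary outcomes in this study include the proportion of responders (PR) and the elimination rate of the main symptom". The abstract gives both the same standing; they "are the primary indicators to evaluate the overall acupuncture effect for PDS". Neither place says whether one success is enough or both are needed.

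**Visits.** Section 2.7.1 gives the same schedule twice: "The measurement of PR will take place at weeks 2, 3, 4, 5, 9, 13, and 17" and "ER will be measured at weeks 2, 3, 4, 5, 9, 13, and 17". Table 2 repeats it and marks no visit as primary.

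**Arms.** Section 2.4 randomises to three groups, the third being the "sham acupuncture plus placebo group in a 1:1:1 ratio".

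**Level and tests.** Section 2.12: "We will establish confidence intervals at a 95% level, with a significance level set at 0.05". Categorical data are to be compared by chi-square or Fisher's exact test. The section names no primary visit or contrast and no order, split or joint rule for the two primaries. It does not mention non-inferiority or the margin.

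**Sizing.** Section 2.11 is specific. It uses the "responder proportion at the end of a 4-week treatment", 70.69% for acupuncture against 55.46% for itopride, with 80% power, one-sided alpha 0.025 and a margin of -10%. It arrives at 57 per group, 67 after 15% dropout and 201 in total. ER does not appear there.

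**The concern.** The sections describe different trials. Section 2.11 is built on one decisive test and spends the whole one-sided 0.025 on PR. Sections 2.7 and 2.12 have two primary outcomes at 0.05 and no rule joining them. The possible rules have different consequences:

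- If either outcome can carry the claim, the chance of a false positive exceeds the nominal level unless alpha is divided, and dividing it costs power.
- If both must succeed, the error is controlled, but the 80% computed for PR alone is only an upper limit on the power to win both.
- If PR at the end of treatment decides alone, the sample size stands, but ER is then not primary in the sense that section 2.7 gives it.

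If the rule stays open until the data are known, the outcome or visit presented as the primary result could be the one that came out best.

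**Working it through.** **Step 1: reproduce the plan's sample size.** Inputs from section 2.11: p_A = 0.7069, p_I = 0.5546, margin 0.10, one-sided alpha 0.025, power 80%.

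- Distance from the margin: 0.7069 - 0.5546 + 0.10 = 0.2523.
- Variance sum: 0.7069 × 0.2931 + 0.5546 × 0.4454 = 0.2072 + 0.2470 = 0.4542.
- n = (1.960 + 0.842)² × 0.4542 / 0.2523² = 56.01, so 57 per group. The Farrington-Manning variance also gives 57.
- Dropout: 57 / 0.85 = 67.06, stated as 67. Strict rounding up gives 68 per group, 204 in total, which is immaterial here.
- Power at 57: standard error = √(0.4542 / 57) = 0.0893, and Φ(0.2523 / 0.0893 - 1.960) = 0.807 (0.800 with pooled null variance).

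The plan's figure is reproduced. It belongs to PR, one visit, one contrast and the full one-sided 0.025.

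**Step 2: error if either PR or ER counts, at one visit and one contrast.** The arms are taken as equal and each test is two-sided at 0.05. If independent: 1 - 0.95² = 9.75%. The article gives no correlation between the outcomes, so a range is assumed. With bivariate normal test statistics:

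| Assumed outcome correlation | At least one p < 0.05 | At least one false result favouring acupuncture (nominal 2.5%) |
|---|---|---|
| 0.3 | 9.5% | 4.8% |
| 0.5 | 9.1% | 4.5% |
| 0.7 | 8.3% | 4.2% |
| 0.9 | 7.0% | 3.5% |

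**Step 3: error if any of the seven visits could also count, one contrast.** There are 2 × 7 = 14 tests. If independent: 1 - 0.95¹⁴ = 51.2%. Two simulations under equality, with assumed correlations:

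- Normal test statistics, the same correlation between all visits, visit and outcome correlations each from 0.9 to 0.3: 15% to 46%.
- Binary outcomes with 67 per arm, rates of 60% and 30%, latent correlation decaying with distance between visits (0.9 to 0.5), outcome correlation 0.7 to 0.3: 34% to 48%.

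Together about 15% to 48%. This step is conditional, because the article does not say that any visit counts.

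**Step 4: cost of an equal alpha split.** With one-sided 0.0125 for each outcome, the critical value is 2.241.

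- Power on PR at 57: Φ(0.2523 / 0.0893 - 2.241) = 0.721.
- n to restore 80%: (2.241 + 0.842)² × 0.4542 / 0.2523² = 67.8, so 68 evaluable. With dropout, 68 / 0.85 = 80 per group, 240 in three arms.

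**Step 5: the section 2.11 test alone.** One test at one-sided 0.025 has an error of 2.5% at the margin. There is no inflation and no change in sample size.

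**The case against.** **The article does point to a lead test.** Section 2.11 names endpoint, time point, contrast, margin and alpha, and section 2.1 names acupuncture against itopride as the comparison. The 95% intervals of section 2.12 match a one-sided 0.025. All of this stands, so a reader who infers that there is no lead endpoint or time point anywhere goes too far. The gap is that endpoint, visit, contrast and margin are absent from the sections that define success and analyse it.

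**A count of 42 primary tests is not supported.** A reader might multiply 2 outcomes × 7 visits × 3 pairwise contrasts and quote an error of 34% to 81% (simulated over assumed correlations). The article gives a schedule of measurements. It does not call each visit confirmatory and sets up no three primary contrasts. Itopride against sham is not an acupuncture claim at all.

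**Two-sided figures under equality are not the error of a non-inferiority test.** This is correct, and they count results against acupuncture too. The favourable-direction column in step 2 answers the second part: 3.5% to 4.8% against 2.5%. It would also apply to non-inferiority if ER had a margin and both true differences lay on their margins, but the article gives ER no margin.

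**Multiplicity detail may sit in an SAP that is not shown.** That is fair for the handling of repeated visits and the sham arm. It does not remove the mismatch between what the article itself fixes: two primaries at 0.05 and a sample size for one test.

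**Conclusion.** The concern holds in a limited form. Two outcomes are declared primary at an unadjusted 0.05, with no stated relation and no deciding visit or contrast in sections 2.7 and 2.12. The single test that justifies 57, 67 and 201 is stated only in section 2.11.

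If either outcome suffices, the two-sided error at one visit and one contrast is about 7% to 10%: a moderate excess that rests on an assumed outcome correlation of 0.9 to 0.3. About 15% to 48% would apply only if any visit could also count, again under assumed correlations. A general statement that the error rate is far above 5% is therefore not supported. On the section 2.11 test alone there is no inflation.

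**What to change.** State in sections 2.7 and 2.12 that the single primary test is PR at the end of treatment (week 5 in Table 2), verum acupuncture plus placebo against itopride plus sham, for non-inferiority with the -10% margin at one-sided 0.025. Make ER at week 5 a key secondary outcome, tested only if PR succeeds. Place the acupuncture against sham comparison in the same pre-specified sequence. Report the other visits as secondary estimates with 95% confidence intervals and no confirmatory claim.

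This changes wording only and leaves 57, 67 and 201 as they are. It should be settled before unblinding. The price is that ER and the follow-up visits can no longer support a stand-alone primary claim. If the sponsor wants ER to keep that status, the alternative is to split alpha and re-size: an equal split needs 80 per group (240 in total) for PR alone, and ER would need a planning rate of its own.

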#### Primary outcome

2.7.1

**The proportion of responders (PR)** Patients experiencing sufficient alleviation of stomach discomfort are categorized as positive responders (23). Participants will be requested to evaluate changes in their symptom relief over the preceding 7 days via a 7-point Likert scale. This scale features options such as “extremely worsened,” “worsened,” “slightly worsened,” “no change,” “slightly improved,” “improved,” or “extremely improved,” which correspond to scores ranging from 0 to 6. Those participants who report a relief score of either 5 or 6 points will be deemed positive responders. The measurement of PR will take place at weeks 2, 3, 4, 5, 9, 13, and 17.

**The elimination rate (ER)** ER refers to the proportion of patients whose main symptoms have disappeared. According to Rome IV criteria, we define postprandial fullness and bloating as the main symptoms. Included patients should have at least one of these symptoms. Using a 7-point Likert scale, the main symptoms are considered to have disappeared if the rating drops to 0 after treatment. ER will be measured at weeks 2, 3, 4, 5, 9, 13, and 17.

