## Introduction

1

Functional dyspepsia (FD) is a common functional gastrointestinal disorder characterized by upper abdominal discomfort or pain without an identifiable organic cause (1). A recent meta-analysis suggests it impacts 8.4% of adults worldwide (2). The Rome IV criteria categorizes FD into three subtypes: epigastric pain syndrome (EPS), postprandial distress syndrome (PDS), and the overlapping form of EPS/PDS (1). PDS, the most common subtype, presents with meal-related symptoms such as postprandial fullness and early satiety. Epidemiological studies from various countries show that PDS accounts for about 60% of FD cases (3, 4) and is more prevalent in Asian populations compared to Western populations (5). Although not life-threatening, the chronic and recurrent nature of FD symptoms significantly impacts patients’ psychological well-being, quality of life (QOL), and social functioning (6). Furthermore, FD imposes a considerable economic burden on patients (7). Therefore, FD has become a significant public health concern requiring heightened clinical attention and research endeavors.

The effective treatment of FD remains an unsolved clinical challenge. FD is recognized as a complex condition with several factors participating in its development (1, 6). Although drugs such as prokinetic agents, acid suppressants, antidepressants, anti-*Helicobacter pylori* medications, and mucosal protectants have been officially recommended for the treatment of FD, single-drug therapy may not address all of the underlying pathophysiological mechanisms of FD, leading to limited efficacy (8). Additionally, these medications may be limited by side effects (9, 10). Therefore, physicians and patients expect more treatments for FD that are both effective and low-risk.

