#### Inclusion criteria

2.3.1

The study will involve individuals who meet the following criteria: (1) aged 18–60 years and long-term residents of Changsha; (2) diagnosed with FD-PDS according to the Rome IV criteria (21): the individual experiences a sense of fullness and some discomfort in the upper abdomen after normal eating and/or a sense of early satiety which influence the completion of the normal dietary intake occurred several times a week (The past 3 months meet the diagnostic requirements, and symptoms should have been present for a minimum of 6 months prior to diagnosis); (3) no structural abnormalities were detected through upper gastrointestinal endoscopy surveillance; (4) non-refractory FD; (5) patients who are *Helicobacter pylori*-negative or have persistent symptoms after *Helicobacter pylori* eradication for 6 months; (6) Good compliance.

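### The elimination rate, a primary outcome, is defined on two different symptom pairs, and one of them does not match the entry criterion

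*Protocol article*

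**What the plan says.** The elimination rate is one of two primary outcomes. Its symptoms are described in these places in the protocol article:

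- **Abstract, Methods:** "the elimination rate of cardinal symptoms (postprandial fullness and early satiation) are the primary indicators".
- **Introduction:** postprandial distress syndrome "presents with meal-related symptoms such as postprandial fullness and early satiety".
- **Section 2.3.1, criterion 2**, which cites Rome IV: a patient qualifies on postprandial fullness "and/or a sense of early satiety which influence the completion of the normal dietary intake". Bloating is not named.
- **Section 2.7.1:** "According to Rome IV criteria, we define postprandial fullness and bloating as the main symptoms". The next sentence adds: "Included patients should have at least one of these symptoms".

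For scoring, section 2.7.1 refers to a 7-point Likert scale without giving its anchors and says that "the main symptoms are considered to have disappeared if the rating drops to 0 after treatment". The outcome is scheduled seven times, from week 2 to week 17. In Table 2 the elimination-rate row has no mark at allocation, whereas the NDSI, SF-NDLQI, HADS, expectation and hormone rows do.

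**The concern.** Two current statements define the same primary outcome on different symptoms. They share postprandial fullness and differ in the second symptom, bloating against early satiation. This is not a detail that a journal article leaves to a fuller document, since a full protocol or analysis plan could agree with only one of the two.

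The difference affects who counts as a success. Section 2.7.1 assumes that every patient enters with fullness or bloating, but criterion 2 does not enforce this. A patient may therefore be enrolled on a symptom that the outcome does not measure. If the choice between the definitions is left until data are available, it becomes a post hoc choice of primary endpoint.

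**Working it through.** **1. Classifying patients under each definition.** I read elimination as both symptoms of the pair rated 0 after treatment. The text does not say so expressly.

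| Patient | Section 2.7.1 (fullness, bloating) | Abstract (fullness, early satiation) |
|---|---|---|
| Enrolled on early satiety alone, no fullness or bloating at entry, early satiety unchanged | Rates 0 on both: eliminated | Not eliminated |
| Fullness and bloating gone, early satiety remains | Eliminated | Not eliminated |
| Fullness and early satiety gone, bloating remains | Not eliminated | Eliminated |
| All three gone | Eliminated | Eliminated |
| Fullness remains | Not eliminated | Not eliminated |

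The definitions disagree in the first three rows, and in both directions. In the first row the section 2.7.1 result is also unrelated to treatment.

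**2. Effect of the first row on the comparison between arms.** Let f be the fraction of patients who enter on early satiety alone and rate 0 on fullness and bloating throughout. Randomisation makes f equal across arms in expectation. Let E be the elimination rate among the other patients in an arm.

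- Observed rate in an arm = f + (1 − f) × E
- Observed difference between arms A and B = [f + (1 − f) × E_A] − [f + (1 − f) × E_B] = (1 − f) × (E_A − E_B)

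The document gives no value for f, so the values below are assumptions:

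| f | Factor on the between-arm difference |
|---|---|
| 0 (the entry statement in section 2.7.1 holds) | 1.00 |
| 10% | 0.90 |
| 20% | 0.80 |

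A stricter reading is that a rating already at 0 cannot drop, so these patients never count as eliminated. The observed rate is then (1 − f) × E, and the difference is again (1 − f) × (E_A − E_B). The level of the rate changes but the shrinkage factor does not.

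**3. The stated sample size.** Section 2.11 uses the responder proportion: 70.69% against 55.46%, margin −10%, one-sided alpha 0.025, power 80%.

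- Variance term: 0.7069 × 0.2931 + 0.5546 × 0.4454 = 0.2072 + 0.2470 = 0.4542
- Distance to the margin: 0.7069 − 0.5546 + 0.10 = 0.2523
- n = 0.4542 × (1.960 + 0.842)² / 0.2523² = 56.01, rounded up to 57 per group
- With 15% dropout: 57 / 0.85 = 67.06, against 67 stated

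The stated 57 is reproduced. The elimination rate does not enter this calculation, so the contradiction changes none of these figures.

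**The case against.** The strongest reply is that bloating in section 2.7.1 is a slip for early satiation, and that the same section guarantees a main symptom at entry, so f is 0. A slip is plausible, but as printed the section is the operative definition of a primary outcome and it credits its pair to Rome IV. The entry statement cannot carry the weight either: criterion 2 decides who is enrolled, and it admits early satiety alone.

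The other side is right to resist several stronger readings that a reader might infer:

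- **That 0 on the elimination scale means extremely worsened.** That anchor belongs to the responder scale, which rates change and whose favourable end is 5 and 6. The elimination text refers to a 7-point scale, not to that one, and a drop to 0 on disappearance makes sense only on a separate severity scale. The anchors may stand in the full protocol.
- **That no baseline rating is taken, so a drop to 0 cannot be determined.** The Table 2 row is a derived post-treatment proportion and could not carry a baseline value. Section 2.2 mentions a baseline assessment. If entry did guarantee a main symptom, a later 0 on both would be enough. A baseline rating matters because the symptom mismatch removes that guarantee.
- **That early satiation is not assessed anywhere.** The NDSI rates 15 upper gastrointestinal symptoms, which the article does not list. The supportable statement is that early satiation lies outside the elimination rate as section 2.7.1 defines it.
- **That the flaw biases the trial toward non-inferiority.** The only stated margin belongs to the responder-proportion calculation, and no expected elimination rates are given. Shrinkage moves a difference toward zero. If acupuncture is better, that makes non-inferiority harder to show; it helps only if acupuncture is worse.

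**Conclusion.** The point holds as a contradiction within the current text. The elimination rate has two incompatible definitions, and the one in section 2.7.1 does not match the population that criterion 2 admits. The conflict can change an individual patient's classification in either direction.

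The only part of the effect that can be expressed is the shrinkage factor 1 − f. It rests on three assumptions: f is equal across arms, these patients rate 0 on fullness and bloating throughout, and they stay in the denominator, as the intention-to-treat rule in section 2.12 implies. The document gives no f and no expected elimination rates, so no loss in percentage points or in power can be stated. The frequency of the other discordant patterns is also unknown.

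The correction is needed because a primary outcome should have one definition before its data are seen. The unprinted scale anchor and the baseline schedule are clarifications that belong with it, not separate errors.

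**What to change.** Amend the protocol before any outcome data are seen:

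1. Use one symptom pair throughout: postprandial fullness and early satiation. This matches the abstract, the introduction and criterion 2. Correct section 2.7.1, including its sentence on which symptoms included patients have.
2. Schedule a rating of these two symptoms at the existing baseline assessment, on the scale used later, and show it in Table 2 as a symptom rating separate from the derived rate.
3. Count a patient as eliminated only if at least one of the two symptoms was present at baseline. State how a patient with neither present is handled, so that the rule fits the intention-to-treat analysis.
4. As a clarification, state that 0 on this scale means symptom absent, to keep it apart from the responder change scale, and that both symptoms must be 0 if that is the intention.

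The cost is a short amendment to the protocol and case report form, with two self-rated items at a visit that already takes place. If the full protocol already collects these ratings, only the text changes. The sample size is unaffected.
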